### 1.8. Optimizing intervention components for sleep promotion

The Multiphase Optimization Strategy (MOST) is an engineer-inspired framework for developing multi-component interventions. MOST has informed a number of multi-component interventions, including: smoking cessation (Piper et al., 2016, 2018; Bernstein et al., 2018; Engle et al., 2019), mental health promotion (Watkins et al., 2016; Uwatoko et al., 2018), physical activity promotion (Celano et al., 2018; Phillips et al., 2018), adult obesity treatment (Pellegrini et al., 2014; Spring et al., 2020), and HIV treatment (Collins et al., 2016; Gwadz et al., 2017). It is ideally suited to determine if digital approaches can be combined and harnessed to improve child sleep duration for the prevention of obesity.

The MOST framework has three phases: (1) the *preparation phase*, to pilot test intervention components; (2) the *optimization phase*, to determine candidate component settings that achieve optimization criteria; and (3) the *evaluation phase*, to determine if the final optimized intervention package is effective using a randomized controlled trial study design (Collins, 2018). With our successful deployment of a mobile health platform to promote sleep in children, we have already completed the preparation phase and are poised to complete the optimization phase (Mitchell et al., 2021). The optimization phase is especially important for developing multi-component interventions as it provides insight into how candidate intervention components operate with respect to primary outcomes. Using highly innovative, efficient and fully powered experimental designs (Collins et al., 2014), optimization trials can determine if each candidate component associates with the primary outcome of interest and can determine if there are interactions between the candidate components with respect to the primary outcome of interest. The extensive knowledge gained provides an opportunity to remove ineffective components, or adjust component settings, so that the final intervention package has been optimized before it is evaluated in expensive randomized controlled trials.

### 1.9. Objective and aims

In this paper we provide the protocol for the Sleep Extension and Enhancement Possibilities for Youth (SLEEPY) 2.0 study. This is an optimization trial designed to determine the optimal component settings for a mobile health platform, for the pediatric care setting, to promote longer sleep duration for childhood obesity prevention. The conceptual model is provided in Figure 1. *Under aim 1*, we will determine the optimal settings for sleep promotion by assessing four candidate intervention components, using a randomized 2^4^ factorial design: (1) a sleep goal component, (2) a digital sleep guidance messaging component, (3) a caregiver-directed incentive component, and (4) a performance feedback component. We hypothesize that we will identify component settings that effectively increase sleep duration. *Under aim 2*, we will determine if the optimal settings for sleep promotion improve fat mass trajectories. Fat mass will be measured at baseline, 6-, and 12-months, and diet intake and behavior will be measured for mechanistic insights. We hypothesize that component settings optimal for sleep will lower gains in fat mass. Finally, *under aim 3*, we will determine if the optimal settings for sleep promotion are equally effective across sociodemographic groups, including the neighborhood context. We hypothesize that component settings that are optimal for sleep will be equitable across sexes, racial/ethnic backgrounds, and neighborhood contexts. Our proposed research will greatly advance the field of behavioral sleep medicine and reimagine how insufficient sleep duration is managed, and obesity is prevented in pediatric healthcare.

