### 3.6. Power calculation

#### 3.6.1. Aim 1

The primary outcome for Aim 1 is nighttime sleep duration (hours per night) on weeknights (measured daily by the sleep tracker). The “MOST” R package (FactorialPowerPlan) was used to determine the sample size needed to detect a 30 min per night difference in nighttime sleep duration on weeknights (alpha = 0.05; power = 0.8; pretest-posttest correlation of sleep duration = 0.7; and a standard deviation sleep duration = 0.7 h per night). The effect size and parameters were derived from our prior studies. The calculation accounted for detection of main effects plus all possible interactions. The power calculation revealed that a minimum sample size of 41 was needed for Aim 1.

#### 3.6.2. Aim 2

The primary outcome for Aim 2 is fat mass index (kg/m^2^) (measured at baseline, 6-months, and 12-months by DXA). The “MOST” R package (FactorialPowerPlan) was used to determine the sample size needed to detect a 0.25 kg/m^2^ reduction in fat mass index at 6-months and 12-months (alpha = 0.05; power = 0.8; pretest-posttest correlation of fat mass index = 0.9; and a standard deviation for fat mass index = 0.9). The effect size and parameters were derived from our prior studies. The calculation accounted for detection of main effects plus all possible interactions. The power calculation revealed that a minimum sample size of 282 was needed for Aim 2.

#### 3.6.3. Aim 3

The primary outcome for Aim 3 is nighttime sleep duration (hours per night) on weeknights (measured daily by the sleep tracker). It has been observed that male children sleep on average 12 min per night less than female children, and that African American/Black children sleep on average 33 min per night less than non-Latinx White children (Guglielmo et al., 2018; Billings et al., 2021; Min et al., 2021). We will determine if the effectiveness of the optimal component settings for sleep promotion differ by ≥20 min across sociodemographic factors. This calculation revealed that 286 participants are needed to detect a ≥20 min per night difference in the effectiveness of the optimal component settings for sleep duration by higher and lower sociodemographic levels. The calculation was completed in Stata (version 14.2) using the “power repeated” command to compute the sample size. The parameters used for the calculation were: alpha = 0.05, power = 0.8, number of repeated measures = 52, number of groups = 2, error variance = 1.1, and correlation = 0.7.

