### 3.7. Statistical plan

Under the intent to treat principle, we will use all available data and participants under the assumption of missingness at random. No participants will be excluded from the analysis except for the unlikely case of no outcome measurements for a participant. Final models will be adjusted for covariate dependent missingness due to dropout. We will examine sensitivity to the assumptions about the missing data mechanism.

#### 3.7.1. Aim 1

Mixed-effects linear regression models will be used to determine if the intervention components are associated with changes in weeknight sleep duration from baseline. The fixed model components will include indicators for each factor (with effect coding used to identify each component level), time in weeks, and all possible interactions between time and factors. The full model will be reduced to a more parsimonious model by selecting the main effects and interactions achieving a Type I error rate of alpha = 0.05.

#### 3.7.2. Aim 2

Mixed-effects linear regression models will be used to measures changes in fat mass index using the most parsimonious model from Aim 1 (i.e., optimal component settings for sleep promotion).

#### 3.7.3. Aim 3

The most parsimonious model from Aim 1 (i.e., optimal component settings for sleep promotion), will be expanded to determine if effectiveness differs by sociodemographic factors. The fixed model components will include indicators for each component (effect coding to represent the levels of each factor), time in weeks, the sociodemographic factor of interest, interactions between time, component(s), and sociodemographic factor. The sociodemographic factors that will be modeled include sex, race/ethnicity, and neighborhood context (poverty, sound, canopy cover, housing and population density, and street connectivity).

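### Aim 3 hypothesizes equity across sociodemographic groups, but is sized and modelled only to detect differences, so a non-significant interaction could be mistaken for support

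*Protocol article*

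**What the plan says.** The protocol article describes Aim 3 in three places.

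- **Section 1.9, objective and hypothesis.** The objective is that "we will determine if the optimal settings for sleep promotion are equally effective across sociodemographic groups, including the neighborhood context", and the hypothesis is that "component settings that are optimal for sleep will be equitable across sexes, racial/ethnic backgrounds, and neighborhood contexts".
- **Section 3.6.3, sample size.** The question becomes one of detection: "We will determine if the effectiveness of the optimal component settings for sleep promotion differ by ≥20 min across sociodemographic factors". The result is that "286 participants are needed to detect a ≥20 min per night difference in the effectiveness of the optimal component settings" between higher and lower sociodemographic levels, from Stata's repeated-measures power command, which sizes a test of difference. The inputs are alpha 0.05, power 0.8, 52 repeated measures, 2 groups, error variance 1.1 and correlation 0.7.
- **Section 3.7.3, analysis.** The Aim 1 model "will be expanded to determine if effectiveness differs by sociodemographic factors", with "interactions between time, component(s), and sociodemographic factor" among the fixed terms.

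The Discussion part of the abstract and section 4 both anticipate that the platform will promote sleep health equity. The 20-min figure appears only as a difference to detect. No margin or interval criterion for concluding equity is given.

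**The concern.** A hypothesis of equal effect is not supported by failing to reject equality. A test of difference returns a non-significant result when the groups truly respond alike, and also when the comparison is too imprecise to tell. The smaller or noisier a subgroup, the more likely a null result becomes. If that null is taken as confirming the hypothesis, imprecision works in favour of the anticipated conclusion.

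At stake is a statement that the selected settings work equally well across sex, race/ethnicity and neighborhood, made while the data remain compatible with differences of the size the protocol itself set out to detect. Those settings are meant to go forward to a later randomized trial.

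**Working it through.** **Inputs from the document.** Section 3.6.3: variance v = 1.1, correlation 0.7, M = 52 measures, difference 20 min = 0.333 h. Section 3.6.1: SD 0.7 h (variance 0.49) and correlation 0.7 for the same outcome. Section 3.6.4: 325 randomized, 10% attrition, so 325 × 0.9 ≈ 292.

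**Assumptions.** Two-sided 5% tests; compound symmetry; one baseline occasion correlated 0.7 with every later one; a component split 1:1; two subgroups with share p in the smaller. The Aim 1 SD is read as a per-night value, in the same way as the 1.1.

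**1. The plan's own figure.** The variance of a mean of 52 measures is 1.1 × (1 + 51 × 0.7)/52 = 0.776. For a two-group difference, N = 4 × 0.776 × (1.96 + 0.842)²/0.333² ≈ 220 (222 with the F test). The stated 286 is not reproduced. That is a separate matter: either figure sizes a test of difference.

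**2. Taking 286 at face value.** The implied SE is 20/(1.96 + 0.842) = 7.1 min, so the 95% half-width is 1.96 × 7.14 = 14.0 min. An estimate just short of significance is about 14 min, with an interval reaching 14 + 14 = 28 min, beyond the protocol's 20. The chance of non-significance is 20% if the true difference is 20 min and 44% if it is 15 min.

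**3. The contrast Aim 3 needs.** A difference between subgroups in a component's effect compares four cells:

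SE² = 4V/(N p(1 − p)), which is 16V/N when p = 0.5.

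The variance V depends on the analysis:
- unadjusted mean: 0.776
- change score: 0.776 + 1.1 − 2 × 0.77 = 0.336
- baseline-adjusted: 0.776 − 0.77²/1.1 = 0.237

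With the Aim 1 variance of 0.49, the same formulas give 0.346, 0.150 and 0.106.

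The chance of missing a true 20-min difference is 1 − Φ(20/SE − 1.96) − Φ(−20/SE − 1.96). At N = 292:

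| Inputs | Split | Analysis | SE (min) | Missed |
|---|---|---|---|---|
| Aim 3 | 50:50 | unadjusted | 12.4 | 63% (64% with a t reference) |
| Aim 3 | 50:50 | change | 8.1 | 31% |
| Aim 3 | 50:50 | adjusted | 6.8 | 17% |
| Aim 3 | 20:80 | unadjusted | 15.5 | 75% |
| Aim 3 | 20:80 | change | 10.2 | 50% |
| Aim 3 | 20:80 | adjusted | 8.5 | 35% |
| Aim 1 SD | 50:50 | unadjusted | 8.3 | 32% |
| Aim 1 SD | 50:50 | change | 5.4 | 4% |
| Aim 1 SD | 50:50 | adjusted | 4.6 | 1% |

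**4. Could equity within ±20 min be shown?** The 90% half-width is 1.645 × SE. With the Aim 3 inputs and equal subgroups it is 20.4 min (unadjusted), 13.4 (change) and 11.3 (adjusted). If the true difference is zero, the chance that the 90% CI lies within ±20 min is 2Φ(20/SE − 1.645) − 1, which is 58% for the change score and 80% with baseline adjustment.

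**The case against.** The protocol never says that a non-significant interaction will be read as equity. Section 3.7.3 gives a model and no decision rule, and alpha = 0.05 is attached only to reducing the Aim 1 model in section 3.7.1. A condensed article may leave the reading of the interaction to an analysis plan that is not shown. This stands: the misreading is a possibility that the text leaves open, not a stated intention. It does not remove the conflict, because the article itself fixes both an equity hypothesis and a sample size and model for difference.

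A reader might also infer that the trial could not show equity within 20 min even if the observed difference were zero. The documents do not support that. It holds only for the unadjusted mean, and narrowly: the 90% half-width is 20.4 min at 292 but 19.3 min if all 325 contribute. The planned model concerns change from baseline, where the half-width is 13.4 or 11.3 min.

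The larger miss rates depend on the Aim 3 variance. The Aim 1 SD for the same outcome gives much smaller ones, and the document states no subgroup shares, so 20:80 is illustrative. Finally, sections 1.8 and 5 leave confirmation of effectiveness to a later trial, and section 4 is a statement of expectation. That limits the consequence without giving this aim a valid test of its hypothesis.

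**Conclusion.** The point holds as a mismatch between hypothesis and inference. Aim 3 states equity; its sample size and model address only detection of a difference; and a null interaction would not show equity.

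Its size depends on the variance. At about 292 completers and equal subgroups, a true 20-min difference goes undetected about 63 to 64%, 31% or 17% of the time with the Aim 3 inputs, and 32%, 4% or 1% with the Aim 1 SD. On the analysis closest to the plan, which models change from baseline, the range is therefore 1% to 31%, and higher where a subgroup is small. Even on the protocol's own 286, a non-significant result can leave differences of up to 28 min open.

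The mismatch itself needs none of these assumptions. The percentages rest on compound symmetry, a single baseline occasion, a 1:1 component split and the subgroup shares shown. It should be corrected before analysis, by wording and analysis changes alone.

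**What to change.** Choose one of two routes.

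**Interval-based rule.** For each sociodemographic factor, report the difference in intervention effect with its CI from the baseline-adjusted model, then conclude as follows:
- Support equity only if the 90% CI (two one-sided 5% tests) lies within a prespecified margin.
- If that holds but the 95% CI excludes 0, report a difference smaller than the margin. The two findings can coincide whenever the SE is below 20/(1.96 + 1.645) ≈ 5.5 min, so the rule must say what happens then.
- Otherwise call the result inconclusive as to equity, and still report a difference where the 95% CI excludes 0.

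The protocol's 20 min is the only candidate margin. It was set as a detectable difference and is two-thirds of the 30-min target in section 3.5.1.1, so the investigators should confirm that it is acceptable as a margin. For race/ethnicity and any other multi-level factor, apply the rule to pairwise contrasts.

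**Rewording.** State Aim 3 as estimating or detecting differences in effect, with CIs, and make no equity claim from a null test. Align the abstract and section 4 accordingly.

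Neither route needs new data or a design change. The cost of the first is that some comparisons, chiefly those with small subgroups, will be labelled inconclusive. The cost of the second is giving up an equity conclusion from this trial.

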**Figure 1 F1:**
[figure not shown]
Conceptual model of candidate component settings and mediators for child sleep promotion and obesity prevention.

## 2. Materials and equipment

### 2.1. Sleep tracker

Participants will be asked to self-monitor their sleep patterns over the entire study period, using an ActiGraph Insight device. The Insight devices are worn on the wrist and use accelerometry to measure arm movements that can infer sleep and wake periods. The data collected on the Insight device will be uploaded into ActiGraph's cloud-based database called CenterPoint using Bluetooth and a smartphone application. The data will be processed in CenterPoint to generate estimates of sleep using the validated Cole-Kripke algorithm for sleep assessment (Cole et al., 1992; Quante et al., 2018). The sleep data will then be transferred to the Way to Health platform using a web API.

### 2.2. Way to health

Way to Health (W2H) is an automated information technology platform that integrates wireless devices, clinical trial randomization, messaging (text and e-mail), and secure data capture for research purposes (Asch and Volpp, 2012). This was designed by faculty and staff at the Leonard David Institute Center for Health Incentives and Behavioral Economics (CHIBE) at the University of Pennsylvania to create an efficient, scalable, and low-cost way to test behavioral interventions using a platform that can be deployed anywhere in the United States. The following features of the W2H Platform will be used in this study: online and mobile participant enrollment; integration with ActiGraph sleep tracker; computerized randomization of participants; automated communication with participants via text; delivery of incentives to encourage behavior change; and online research and electronically secured data.

### 2.3. REDCap

REDCap is a secure, HIPAA-compliant application for data collection and storage that provides logging of all project activity and data entry history for all records, as well as HIPAA-compliant security and daily backups. REDCap will be used for screening potential participants, consenting participants, and delivering surveys to enrolled participants.

## 3. Methods

### 3.1. Study design

A 2^4^-factorial design (i.e., 16 study conditions) will be used to address the study objectives (Table 1). A two-week run-in phase will be used to measure baseline sleep duration, a 6-month intervention phase will be used to measure changes in sleep duration from baseline, and a ≈5.5-month follow-up phase will be used to measure if there are lasting changes in sleep duration from baseline. Clinical measurements (e.g., DXA, 24 h dietary recalls) will be obtained at baseline, 6-months, and 12-months at the Children's Hospital of Philadelphia (CHOP).

**Table 1 T1:** The 2^4^ factorial study design.

	**Candidate components**			
**Condition**	**Sleep goal**	**Digital messaging**	**Caregiver incentive**	**Performance feedback**
1	≥9 h	Active	Inactive	Inactive
2	≥9 h	Active	Inactive	Active
3	≥9 h	Active	Active	Inactive
4	≥9 h	Active	Active	Active
5	≥9 h	Active + SA	Inactive	Inactive
6	≥9 h	Active + SA	Inactive	Active
7	≥9 h	Active + SA	Active	Inactive
8	≥9 h	Active + SA	Active	Active
9	≥30 min above baseline	Active	Inactive	Inactive
10	≥30 min above baseline	Active	Inactive	Active
11	≥30 min above baseline	Active	Active	Inactive
12	≥30 min above baseline	Active	Active	Active
13	≥30 min above baseline	Active + SA	Inactive	Inactive
14	≥30 min above baseline	Active + SA	Inactive	Active
15	≥30 min above baseline	Active + SA	Active	Inactive
16	≥30 min above baseline	Active + SA	Active	Active

SA, Sleep Advisor.

### 3.2. Sample

The sample will include 325 typically developing children and one of their caregivers. To be eligible the children must be aged 8–12 years, have a body mass index (BMI) greater than or equal to the 50^th^ and less than the 95^th^ percentile, and typically sleep <8.5 h per night. Children will be excluded if they have a diagnosis of a major medical condition and/or take medications that impact sleep. Caregivers must be available to put their child to bed on the majority of nights during the study and have smartphone, tablet, or computer access for the duration of the intervention. Table 2 lists the full inclusion and exclusion criteria. Eligibility will be assessed using a screening questionnaire, with the exception for BMI, which will be assessed using measured height and weight at the baseline study visit, and sleep duration, which will be assessed during the run-in phase.

**Table 2 T2:** Inclusion and exclusion criteria for children and caregivers by eligibility assessment phases.

**Screening phase inclusion criteria for children**	**Children aged 8 to 12 years**
	Speak, read, and write in English
	Parental/guardian permission (informed consent) and child assent
Screening phase exclusion criteria for children	A clinically diagnosed chronic disease falling under one or more of the following categories: congenital birth defects, syndromes, or abnormalities; cardiac, hematological, oncological, immunological, pulmonary, renal, rheumatological, or musculoskeletal conditions; endocrine, gastrointestinal, metabolic, sleep, neurodevelopmental, or weight disorders
	Children regularly taking medications related to exclusionary medical conditions or that impact sleep
	Children who will transition to high school during the study
	Children who share a bed
	Children enrolled in another clinical trial
	Have a parent/guardian works, or has a family member who works, for the Division of Gastroenterology, Hepatology and Nutrition at CHOP
Screening phase inclusion criteria for caregivers	Be the parent/guardian of an eligible child enrolled in the main study
	Speak, read, and write in English
	Be available to but the child to bed on the majority of nights
	Have access to a smartphone to install the sleep tracking application for the duration of the study
Baseline study visit inclusion criteria for children	BMI ≥ 50^th^ and <90^th^ percentile for age and sex
Run-in period inclusion criteria for children	Sleep duration ≤ 8.5 hours per night on average

BMI, Body Mass Index; CHOP, Children's Hospital of Philadelphia.

### 3.3. Study timeline

The study will be conducted in 5 phases: screening, run-in, randomization, intervention, and follow-up. The study procedures occurring during each phase are illustrated in Table 3, and the study activities completed during each study phase are described below.

**Table 3 T3:** Study procedures across the 12-month study period.

**Study phase**	**Screening**	**Run-In**		**Rand**.	**Intervention**							**Follow-up**						
**Where**	**Home**	**CHOP visit 1**	**Home**	**Home**	**Home**						**CHOP visit 2**	**Home**						**CHOP Visit 3**
**Study month**	**N/A**	**0**	**0^a^**	**0**	**1**	**2**	**3**	**4**	**5**	**6**	**6**	**7**	**8**	**9**	**10**	**11**	**12**	**12**
Screening questionnaire	X																	
Informed consent/assent		X																
Anthropometry		X^b^									X							X
DXA scan		X^c^									X							X
Child and caregiver questionnaires		X									X							X
Wear sleep tracker			X^d^		X	X	X	X	X	X	X	X	X	X	X	X	X	X
Sleep diary			X			X		X		X			X		X		X	
Dietary recall			X						X							X		
Randomization (if eligible)			X	X														
Intervention engagement					X	X	X	X	X	X								
Monthly surveys					X	X	X	X	X	X	X^e^	X	X	X	X	X	X	X^e^

^a^Data will be collected during the 2nd week of the run-in period. ^b^Confirm BMI eligibility from the baseline anthropometry measures. ^c^Pregnancy tests will be administered to female participants who are 11 years and female participants younger than 11 years who have begun menses. ^d^Confirm insufficient sleep duration eligibility from sleep tracker data collected during the run-in phase. ^e^Monthly survey items will be completed at Visit 2 or Visit 3 if the surveys were not completed at home during months 6 or 12, respectively.

#### 3.3.1. Visit 1

Participants who pass the screening questionnaire will be invited to CHOP for an in-person study visit. Prior to any research procedures, the caregiver and child will complete the informed consent/assent process. As the first procedures, height and weight measures will be taken to determine BMI eligibility. Next, the sitting height and waist circumference measures will be measured, followed by the DXA scan and questionnaires. The caregiver will also complete questionnaires. Before leaving, the caregiver will be provided with a W2H account and the child will be given a sleep tracking device. A smartphone application that is needed to collect the sleep tracker data will be installed on the caregiver's smartphone, tablet, or computer.

